### 2.4. Sample Size Calculation

The sample size was calculated using the Grayling and Wason method for multi-arm trials [56], which is appropriate for a design with two experimental groups and one control group. A medium effect size (Cohen’s d = 0.5) and homogeneity of variance (σ = 1) were assumed across groups as recommended [57] when no clear estimate on this association is provided in the available studies with similar design [48,49]. With a two-sided α of 0.05 and 80% power (β = 0.20), the required sample size was obtained via the “des_ss_norm()” function in R statistical software, version 4.5.2 (R Core Team, 2024, Vienna, Austria). All three arms were allocated at a 1:1:1 ratio. To account for multiple comparisons, the Benjamini–Hochberg correction was applied to control the false discovery rate. The power calculation was based on a disjunctive criterion, which estimates the probability of detecting at least one significant difference between any intervention group and the control group. The initial calculation yielded a requirement of 42 participants per group. After accounting for an anticipated 20% dropout rate, the final sample size was adjusted to 53 participants per group. This resulted in a total target enrollment of 159 participants across all three study arms. The participants will initially be drawn from the 463 students enrolled in the Nuts4Brain-Z observational study (data collection September–December 2023) [58,59,60]. If necessary, recruitment will be extended to additional UCLM undergraduate students to reach the target sample size.

The sample size calculation was based exclusively on the primary outcome as we did not find previous studies examining the association between nut consumption and our secondary outcomes that would provide the necessary effect size estimates for power and sample size calculations. Consequently, the study should be considered exploratory with regard to these secondary outcomes, and any findings related to them should be interpreted with appropriate caution. While our sample size provides adequate power for detecting changes in the primary outcome, we acknowledge that it may be underpowered for detecting meaningful differences in secondary outcomes, particularly if the true effects are small to moderate in magnitude.

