Stress: Perceived stress levels will be measured using the 10-item Perceived Stress Scale (PSS-10) [69,70], a widely validated self-report instrument designed to assess the degree to which individuals appraise situations in their lives as stressful over the previous month. Each item is rated on a 5-point Likert scale ranging from 0 (“never”) to 4 (“very often”), resulting in a total score between 0 and 40, where higher scores indicate greater perceived stress. Validation studies have reported satisfactory internal consistency for the Spanish version of the PSS-10 (α = 0.82) [70]. Since no validated cutoff scores exist for the PSS-10, it will be analyzed as a continuous variable, and the study sample will be classified into tertiles for comparative analysis.

Cognition: Cognitive performance will be evaluated at the 4 assessments with the National Institutes of Health (NIH) Toolbox Cognition Battery (Chicago, IL, USA), which is administered on an iPad by trained personnel. This widely used computer-based method has been normed for children and adults aged 3–85 years [71]. Specifically, the Fluid Cognition Composite Score will be measured [71], as it is more sensitive to changes resulting from lifestyle interventions than is crystallized cognition [72]. This composite score assesses executive function, processing speed, working memory, episodic memory, and attention through five individual test instruments (~30 min), including the Flanker Inhibitory Control and Attention Test (Flanker) (inhibitory control and attention), the Dimensional Change Card Sort (DCCS) (cognitive flexibility), the Picture Sequence Memory Test (PSMT) (episodic memory), the List Sorting Working Memory Test (LSWM) (working memory), and the Pattern Comparison Processing Speed Test (PCPST) (processing speed). Equivalent alternate forms of the subtests will be administered during follow-up assessments to minimize practice effects. Age-standardized scores for each evaluation and the fluid composite score will be used as the main outcomes of cognitive function. The age-adjusted fluid cognition composite score of the Spanish NIH Toolbox has shown good reliability (ω = 0.78) [73] and moderate to strong convergent validity with established neuropsychological measures [73].

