The results will be considered statistically significant at the α = 0.05 level. In the presence of statistically significant effects, post hoc analyses will be conducted using a pairwise comparison test to delineate specific contrasts between each intervention group and the control arm. Furthermore, statistical and clinical significance will be distinguished in our discussion, considering both the magnitude of effects and their potential implications for guidelines recommending nut consumption as a strategy to prevent or improve mental health outcomes. Therefore, when the estimators of associations do not reach statistical significance due to the small difference between the intervention and control groups, the results will be presented for their descriptive value and to inform future RCTs exploring the relationship between nuts and mental health. Although *p*-values are relevant, changes that are not statistically significant can still be clinically meaningful [104].

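### Section 2.11 tests several primary outcomes at 0.05 with no correction across them, whereas the sample size assumed one primary outcome with Benjamini–Hochberg-corrected dose contrasts

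*Protocol article*

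**What the plan says.** **Sample size (section 2.4).** The trial is sized on one outcome: "The sample size calculation was based exclusively on the primary outcome". The assumptions are: "A medium effect size (Cohen’s d = 0.5) and homogeneity of variance (σ = 1) were assumed across groups". The comparisons are each nut arm against control, power means detecting at least one such difference, and "To account for multiple comparisons, the Benjamini–Hochberg correction was applied to control the false discovery rate". The result is 42 per group, raised to 53 for dropout (159 in total).

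**Outcomes.** Section 2.10.1 and Table 1 list four primary outcomes: BDI-II, GAD-7, PSS-10 and cognition. The abstract lists these and BDNF, which section 2.10.3 and Table 1 place among the confounding, mediating and moderating factors. On cognition, section 2.10.1 says: "Age-standardized scores for each evaluation and the fluid composite score will be used as the main outcomes of cognitive function". It describes five tests, and Table 1 shows those five as the primary cognitive measure.

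**Decision rule (section 2.11).** "The results will be considered statistically significant at the α = 0.05 level". Then: "In the presence of statistically significant effects, post hoc analyses will be conducted using a pairwise comparison test", to compare each nut group with control. No lead outcome is named. The only multiplicity adjustment in this section is for the BDNF–cognition analyses, which it labels secondary or exploratory.

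**The concern.** The sections describe two different trials. One has a single primary outcome and two corrected contrasts. The other has four or five primary outcomes (nine or ten scores if each cognitive test counts), each judged at 0.05. The exploratory BDNF work is adjusted and the primary family is not.

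Under the rule as written, a positive result on any one of the scales could be presented as a primary finding, and the chance of a false one is several times 5%. The 5% level used to size the trial then no longer describes the trial's claim. Because no lead outcome is named, nothing in the article limits which result is put forward.

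**Working it through.** **1. The plan's own figure.** Inputs from section 2.4: d = 0.5, σ = 1, 1:1:1 allocation, BH over two contrasts, at least one rejection. Each contrast is z = (nut mean − control mean)/√(2/n). At n = 42 its expected value is 0.5/√(2/42) = 2.29, and the two contrasts correlate 0.5 through the shared control. BH rejects at least one if the smaller p ≤ α/2 or the larger p ≤ α. Simulated with known variance:
- one-sided α = 0.05: power 80.2%, required n = 42, which matches the plan;
- two-sided α = 0.05, as stated: power 70.1%, required n = 54.

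So 42 reproduces as a single-outcome BH calculation, but only one-sided. That is a separate sample-size matter. Dropout: 42/0.8 = 52.5, rounded up to 53; 53 × 3 = 159.

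**2. Number of primary scores.** Three scales plus one cognitive score = 4; with BDNF, 5. Three scales plus five tests plus the composite = 9; with BDNF, 10.

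**3. Error under no effect on any outcome, one overall test per outcome.** For independent outcomes the chance of at least one significant result is 1 − 0.95^k:
- k = 4: 18.5%
- k = 5: 22.6%
- k = 9: 37.0%
- k = 10: 40.1%

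For correlated outcomes I simulated 200,000 trials: three arms, equal correlation, one time point, and a 2-df test per outcome, n·Σ(arm mean − grand mean)² > 5.99. The documents give no correlations, so 0 to 0.5 is an assumption.

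| Rule | 4 outcomes | 5 outcomes | 9 scores |
|---|---|---|---|
| Any overall test significant | 16–18.5% | 19–23% | 27–37% |
| Overall test and a nut-versus-control contrast, both at 0.05 | 13–16% | 16–19% | 24–32% |
| Same, contrast in favour of nuts | 7–8% | 8–10% | 12–17% |
| Dose contrasts tested directly at 0.05, uncorrected | 27–32% | 31–38% | 44–57% |
| BH over all outcome-by-dose p-values | 4.5–4.9% | 4.5–4.8% | 4.2–4.9% |

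Within one outcome the gate does not inflate error: the chance of any false contrast is 4.1%. The excess arises across outcomes.

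**4. The gate and power.** One outcome, n = 42, two-sided 0.05, known variance, power to find at least one dose:
- both doses d = 0.5: gated 65.6%, direct BH 70.1%;
- one dose d = 0.5, the other 0: gated 58.0%, direct BH 53.5%.

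The overall test has the same noncentrality in both cases, 42 × 0.1667 = 7.0. The comparison therefore turns on how the contrasts behave, and its direction reverses.

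**The case against.** **A protocol article condenses.** BH is named in section 2.4, section 2.11 does not withdraw it, and detailed multiplicity procedure often sits in a fuller plan. This has weight for detail. But the article itself states the level, the post hoc ordering, the list of primary outcomes and the single-outcome basis of the sample size, and these do not agree. BH over two contrasts would also leave several outcomes uncovered.

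**The overall test is an inference.** Section 2.11 does not use the term, and it also says interpretation will focus on the fixed-effects coefficients, which could be the dose contrasts themselves. That stands as a caveat. It does not help the plan, because untreated direct contrasts give 27–32% for four outcomes.

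**The count of nine can be disputed.** Section 2.8 uses the word evaluations for visits, so the cognition sentence may mean each visit and not each test. Table 1 favours the test reading. The 37% is also a ceiling: the composite is built from the five tests, so zero correlation among all nine scores is impossible.

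**Stronger readings the documents do not support.** A reader might infer that a null trial would probably report a primary benefit. A false benefit after the gate is about 7–8% for four outcomes and 12–17% for nine scores. A reader might also infer that the gate necessarily loses power, but the scenarios above go both ways. Nor does the article say that each visit is tested separately, so a further increase from repeated visits cannot be claimed.

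**Conclusion.** The point stands as an inconsistency that leaves the primary family uncontrolled. As written, the chance of at least one significant primary outcome when nothing works is roughly three to five times 5%: about 16–18.5% with four outcomes, 19–23% with five, and up to 27–37% if nine scores count. Requiring a significant nut-versus-control contrast as well lowers this to 13–16% for four and 24–32% for nine.

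These figures assume one overall test per outcome, a single time point, known variance and equal correlation between 0 and 0.5. The gate is a mismatch with the sample-size assumptions, but its effect on power is modest and depends on the scenario. It is not the main defect.

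**What to change.** 1. Settle the primary set and state it identically in the abstract, section 2.4, section 2.10.1 and Table 1, including whether BDNF is primary.
2. Keep the fluid composite as the only primary cognitive score and make the five test scores secondary.
3. In section 2.11, estimate the two dose-versus-control contrasts at 6 months directly from the mixed model, without a prior overall test. Apply the BH correction already named in section 2.4 across all primary-outcome-by-dose p-values: 4 × 2 = 8, or 5 × 2 = 10 if BDNF stays primary.
4. Alternatively, name one primary outcome, as section 2.4 implies, apply BH to its two contrasts, and make the rest secondary.

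**Cost.** With BH over eight tests, a lone effect in one outcome and one dose must reach about 0.05/8 = 0.00625 (0.05/10 = 0.005 with ten), against 0.05/2 = 0.025 with a single primary outcome. If only one of four outcomes responds, at d = 0.5 in both doses, it is in effect tested at 0.05/4. Power at 42 per arm is then about 49%, against 70% with a single primary outcome. Option 4 avoids that loss. BH controls the false discovery rate, so it equals control of any false finding only when no outcome is affected.

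This is more than an edit of wording: it changes the status of outcomes, and section 2.12.2 requires ethics approval before an amendment. The Introduction places the article before recruitment and data collection, so the choice can still be made without sight of data.

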The Nuts4Brain-RCT provides several distinctive contributions beyond existing trial designs. In contrast to previous studies, which have primarily focused on preventing cognitive decline and dementia in older adults [37,47] or have relied on observational evidence [17,18], this protocol targets young adults aged 18–24 years, a critical developmental period for mental health [48,49]. Regarding the three available RCTs on nut consumption and mental health associations in young populations, Pribis et al. [50] examined the effects of walnut consumption (1/2 cup or 60 g) on mood and cognitive performance among young adults. They found a significant medium effect size improvement in mood among males (Cohen’s d = 0.708, *p* = 0.043), but no significant changes were found for females or when both sexes were combined, as observed in another article with data from the same RCT [51]. Additionally, an increase in inferential verbal reasoning (d = 0.567; *p* = 0.009) was found, but no significant increases were detected in memory or non-verbal reasoning ability [50]. Herselman et al. (2022) [48] examined the effects of daily walnut consumption (56 g/day for 16 weeks) and academic stress on mental health in university students. A significant decrease in feelings associated with depression was found in women who consumed walnuts compared to controls; however, male data were not analyzed due to low participant numbers. In addition, Pinar-Martí et al. [49] studied the effect of walnut consumption (30 g/day for six months) on neuropsychological development in adolescents. Although no improvements in neuropsychological function were found when comparing the intervention and control groups, some benefits were observed in variables such as sustained attention and fluid intelligence among participants with better adherence to the intervention. The key methodological innovation is the dose–response design (30 g/day vs. 60 g/day), addressing the current lack of evidence on optimal nut intake for mental well-being. Moreover, whereas many prior trials have assessed isolated outcomes, this study adopts a comprehensive and integrative approach by combining psychometric assessments, objective cognitive testing, and biological markers related to underlying mechanisms. Finally, the inclusion of a 12-month follow-up (comprising a 6-month intervention and a 6-month post-intervention period) allows for the evaluation of the sustainability of effects, thereby distinguishing this protocol from shorter-term interventions.

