### 2.11. Data Management and Statistical Analysis Plan

The principal investigator will have exclusive responsibility for the data and will retain an offline copy on a secure hard drive. The anonymized data will be stored in an open-access repository (Zenodo.org) and may be shared with other researchers upon reasonable request.

The initial analytical approach will comprise descriptive statistics and data visualization to perform an exploratory assessment of the dataset, including an evaluation of bivariate associations between the predictor variables (nut consumption doses) and the outcome variables (mental health parameters). This stage will assess potential baseline differences among the three groups (CG, IG-30, and IG-60).

Subsequently, assumptions of normality and homoscedasticity for the outcome variables will be examined to ascertain the suitability of employing a repeated-measures mixed-effects model to characterize the intervention relationship between nut consumption and mental health indicators. Interpretation will focus on the magnitude and statistical significance of the fixed effects coefficients, thereby determining whether nut consumption is associated with changes in mental health outcomes and whether these associations vary across study intervention groups.

The role of BDNF will also be analyzed, examining associations between BDNF changes and mental health measures through correlation analysis at each timepoint, mediation analyses using structural equation modeling to test whether BDNF mediates the relationship between nut consumption and mental health, including cognitive improvements, and dose–response analyses across study arms. Secondary exploratory analyses will include responder analyses (BDNF increase), time-course analyses using linear mixed models, and interaction analyses examining moderators such as baseline BDNF levels and mental health status. All BDNF-cognition analyses will be designated as secondary/exploratory with appropriate adjustments for multiple comparisons and covariates, including age, sex, baseline cognitive performance, physical activity, and dietary quality.

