### 2.12. Limitations and Contingency Plan

#### 2.12.1. Limitations

The study uses a single-blind design because participants cannot be blinded to nut consumption. This may introduce expectancy bias, but it is mitigated by blinding outcome researchers. Primary mental health outcomes rely on self-report questionnaires and are therefore subject to reporting biases. However, validated instruments and complementary objective measures, such as cognitive tests and biomarkers, are included. Adherence cannot be directly observed in free-living conditions. Monitoring through biweekly contact and determination of vitamin E blood concentrations at each visit improves, but does not guarantee, compliance and does not prevent contamination of the control group. The sample consists of university students aged 18–24 years from a single campus. This limits generalizability but enhances internal validity in an understudied population. The study may be underpowered for small effects, secondary outcomes, or subgroup analyses, particularly if dropout exceeds the anticipated 20%. Finally, the 6-month intervention and follow-up period may be insufficient to assess long-term or delayed effects.

The extensive assessment protocol may increase participant burden and the risk of attrition. Although a validated FFQ will be used, dietary assessment remains imprecise and is subject to underreporting and recall bias. Additionally, some control group participants may live with participants from other study groups, which makes complete prevention of contamination unrealistic. While the CG will be instructed to avoid nuts from any source and the IG-30 and IG-60 groups will be instructed to avoid nuts from non-study sources, accidental or intentional nut consumption may still occur.

Finally, academic stressors (e.g., exams, tight assignment deadlines) and seasonal variations may affect mental health and thereby influence the study associations.

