Specifically, daily consumption of 30 g of mixed nuts for six months is expected to result in a decrease in the frequency, severity, and number of depressive symptoms and a reduction in anxiety and stress levels, alongside improvements in mental well-being, cognitive function, and sleep quality. The participants who will consume 60 g/day are anticipated to demonstrate a modest increase in these benefits, reflecting a potential dose–response effect. This hypothesis is based on biological plausibility, suggesting that a higher intake of certain compounds (e.g., polyphenols and omega-3 fatty acids) may exert stronger anti-inflammatory, antioxidant and neuroprotective effects required to modulate brain function [19,23]. Additionally, the intervention is expected to improve overall diet quality, maintain body weight (with possible minor reductions in body fat percentage and waist circumference), and enhance metabolic health, including improved lipid profiles, lower blood glucose levels, and reduced inflammatory markers, compared with those of the control group.

This protocol presents several key strengths. First, its randomized controlled design with a dose–response approach addresses a critical evidence gap regarding the “optimal dose” of nut consumption for enhancing mental well-being. Second, the study adopts a multidisciplinary assessment strategy that integrates validated psychometric scales (BDI-II, GAD-7), comprehensive neuropsychological evaluations, and biochemical validation (BDNF). Third, the intervention extends over a six-month period, providing a sufficiently long timeframe to observe meaningful effects. In addition, a fourth visit will be carried out six months after the end of the intervention to evaluate whether nut consumption and its potential effects persist over time. Fourth, adherence will be rigorously monitored through the provision of prepacked nut portions and objective verification via plasma vitamin E levels, thereby increasing compliance in a manner that overcomes challenges typically associated with dietary interventions. Finally, relevant variables (habitual dietary intake, physical activity, fitness, etc.) will be examined for moderating, mediating, or confounding effects.

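### The 30 versus 60 g/day question is the stated innovation, but no named contrast for the mental-health and cognitive primary outcomes separates the two doses

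*Protocol article*

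**What the plan says.** The Introduction sets the aim: "The key methodological innovation is the dose–response design (30 g/day vs. 60 g/day), addressing the current lack of evidence on optimal nut intake". The Discussion adds a directional hypothesis, that those on 60 g/day are "anticipated to demonstrate a modest increase in these benefits, reflecting a potential dose–response effect", and lists the question of the best dose first among the strengths. No size is given for the extra benefit.

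Section 2.11 describes a repeated-measures mixed model whose fixed effects are to show, among other things, "whether these associations vary across study intervention groups". The abstract likewise says that the models will estimate effects of consumption and of dosage. Neither place names a contrast. The pairwise comparisons that are named come after a statistically significant effect and are meant "to delineate specific contrasts between each intervention group and the control arm". The phrase "dose–response analyses across study arms" does occur in 2.11, but inside the sentence on the role of BDNF and without a method.

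Section 2.4 bases power on a disjunctive criterion, at least one intervention group differing from control, with d = 0.5, SD 1, 42 evaluable per group and 53 enrolled per group.

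**The concern.** The quantity that the protocol advertises is the difference between 60 g and 30 g. The contrasts it names, and the power calculation behind them, all have the control arm on one side. Evidence that each dose beats control, or that one does and the other does not, does not answer whether 60 g does more than 30 g.

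At stake is the trial's main claim to novelty. With no dose contrast fixed in advance, the report may give two comparisons with control and leave readers to judge dose by eye. A dose comparison chosen after the data are seen would carry less weight than one named now. The article states that it precedes recruitment, so the choice can still be made cleanly.

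**Working it through.** **Inputs.** From section 2.4: d = 0.5, SD 1, two-sided 0.05, Benjamini–Hochberg (BH), 1:1:1, 42 evaluable per group, 20% dropout. From section 2.11: dose-versus-control comparisons after a significant effect. The true 60 minus 30 g difference is not given, so a range is assumed.

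**1. The plan's own figure.** 42 / (1 − 0.20) = 52.5, rounded up to 53, and 3 × 53 = 159; both match 2.4. The 42 itself reproduces for disjunctive power with BH only at one-sided 0.05 (power 0.802). At two-sided 0.05, 42 per group gives 0.700 and 54 are needed. That is a separate matter; 42 is used below because it is the plan's number.

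**2. Would a linear trend supply the missing contrast?** Centred doses are −30, 0 and +30. With equal arms the slope is 30 × (mean60 − mean0) / (30² + 0² + 30²) = (mean60 − mean0) / 60. The 30 g mean drops out. The trend test is the 60 g versus control comparison, which 2.11 already names, and it cannot tell a plateau at 30 g from a further gain at 60 g.

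**3. What reading dose from significance would do.** Simulation: 400,000 trials, 42 per arm, means 0 / 0.5 / 0.5 (the doses are identical), pooled t-tests.

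| Rule | Exactly one dose significant | Only 60 g significant |
|---|---|---|
| Overall test first, then p < 0.05 | about 19% | about 9% |
| BH over the two comparisons | about 22% | about 11% |
| No adjustment | about 31% | about 16% |

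The two nut arms are exchangeable here, so the last column is half of the one before it. Only that half agrees with the protocol's hypothesis.

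**4. Precision of 60 g minus 30 g.** Unadjusted, at one time point, with 42 per arm: half-width = t(0.975; 123) × √(2/42) = 1.979 × 0.218 = 0.43 SD. If baseline is adjusted for with correlation r (assumed), multiply by √(1 − r²):
- r = 0.5: 0.43 × 0.866 = 0.37 SD
- r = 0.7: 0.43 × 0.714 = 0.31 SD

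**5. Power of that contrast.** Two-sided 0.05, unadjusted, 42 per arm:
- true difference 0.1 SD: about 7%
- 0.2 SD: about 15%
- 0.3 SD: about 27%

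For 80% power the normal approximation needs 393 per arm at 0.2 SD and 175 per arm at 0.3 SD. The difference detectable with 80% power at 42 per arm is (1.960 + 0.842) × √(2/42) = 0.61 SD. That exceeds the 0.5 SD assumed for a whole dose-versus-control effect.

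**The case against.** The strongest reply is that the plan does address dose. Section 2.11 looks for variation across the intervention groups, the abstract speaks of dosage, and in a model with group terms the 60 minus 30 g difference is a linear combination of coefficients that will be fitted anyway. A journal article need not list every contrast. All of this stands to the extent that the quantity is obtainable and the intent visible. It does not remove the mismatch. Section 2.11 does say which pairwise contrasts will be made, and the one that matches the stated innovation is not among them.

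A reader might go further and infer that the protocol will declare a dose effect when one dose is significant and the other is not, or that it cannot estimate the dose difference at all. The text supports neither. No section states such a rule. Section 2.11 says that non-significant results will still be presented and that magnitude will be weighed, which points away from comparing verdicts.

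Three further points stand. The 19% to 22% counts both directions; only about half favours 60 g. The 0.43 SD half-width is for an unadjusted comparison of completers and is not the precision of the planned mixed model. Low power is partly disclosed: section 2.12.1 warns about small effects and the Discussion claims power for medium ones, though neither mentions the dose contrast.

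One could add that comparing the nut arms with each other avoids the expectancy problem raised in 2.12.1. That contrast may be less exposed, but participants know whether they receive 30 g or 60 g, so it is not free of it. The point does not rest on this.

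**Conclusion.** The concern holds as a mismatch between aim and named analysis: for depression, anxiety, stress and cognition, nothing stated separates 60 g from 30 g. The error rates in step 3 describe a risk that the protocol leaves open to its readers, not a procedure that it adopts. They assume equal true effects of d = 0.5 and 42 evaluable per arm.

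Naming the contrast will not make the trial decisive on dose. If modest means 0.2 to 0.3 SD (an assumption), the study has roughly a 15% to 27% chance of detecting it unadjusted, and somewhat more if baseline adjustment helps. An interval of about ±0.3 to ±0.4 SD is what the trial can offer. The change should be made before recruitment, but it does not threaten the dose-versus-control comparisons.

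**What to change.** - **Section 2.11:** pre-specify the IG-60 minus IG-30 contrast at 6 months, from the same mixed model, for each primary outcome. Report the estimate with its 95% CI whether or not the overall test is significant, and state that conclusions about 60 g versus 30 g rest on that estimate.
- **Section 2.4:** state that the trial is not powered for this contrast. Any precision quoted should carry its basis: about 0.43 SD half-width unadjusted with 42 per arm, and about 0.31 to 0.37 SD under baseline adjustment with an assumed correlation of 0.5 to 0.7. Label the power figures as resting on assumed differences.
- **Introduction and Discussion:** replace the language about finding an optimal dose with estimating the difference between the two doses.

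The cost is one more contrast per outcome from a model already planned, and a few sentences. Sample size, visits and measurements do not change.
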